The primary outcome measure “CCI®” will be expressed as means (standard deviations) or medians (interquartile ranges) and will be tested for non-inferiority using independent samples *t*-test or Mann–Whitney *U* test, as appropriate dependent of the distribution. The most important secondary outcome measure “time to functional recovery” will be measured in days and will be tested for superiority using the Wilcoxon (Gehan-Breslow) test or log-rank test, depending on the distribution. Secondary analysis will include correction for censored patients (death before time to functional recovery obtained). For the primary study outcome, the lower limit of the two-sided 95% confidence interval of the difference in proportions will be reported and compared with the non-inferiority margin. Additionally, the individual functional recovery criteria will be analyzed separately. Major complications, expressed in proportions, will be tested for non-inferiority using chi-square or Fisher’s exact test as appropriate. The distribution of variables will be determined using several plots (boxplot, Q-Q plot and histogram) and the Kolmogorov–Smirnov and Shapiro–Wilk tests. For comparison of normally distributed continuous variables, the independent samples *t*-test will be used, and values will be expressed as means (standard deviations). Continuous non-normally distributed variables will be compared using the Mann–Whitney *U* test, and values will be expressed as medians (interquartile ranges). Categorical variables will be compared by chi-square or Fisher’s exact test as appropriate, and values will be expressed as proportions. A two-tailed *p*-value < 0.05 will be considered statistically significant. Time to event endpoints, such as survival, will be calculated using Kaplan–Meier estimations. A Cox regression analysis will be performed to investigate predictors of postoperative survival. All parameters with a *p*-value < 0.1 in a univariable analysis will be included in the multivariable Cox regression analysis. Additionally, multivariable analyses will be performed to determine predictors for primary and secondary study outcomes, for example the occurrence of major complications, postoperative pancreatic fistula, and R0 resection. Furthermore, predictors for receiving adjuvant chemotherapy or readmission will be assessed.

For subjects who are lost to follow-up, a sensitivity analysis will be performed to determine best case/worst case scenarios.

The following pre-specified subgroup and sensitivity-analyses will be performed:Comparing MIPD and OPD in patients with major complications (Clavien-Dindo grade ≥ III) and without major complications (no complication or Clavien-Dindo I-II) separatelyComparing centers for low and high annual MIPD volume during the trial separately (< 20 MIPD/year versus ≥ 20 MIPDs/year)Comparing MIPD and OPD in patients with pre-malignant indications and PDAC separately.Comparing incidence of POPF in MIPD and OPD for the ISGPS subgroups of POPF risk and the A-B-C variant [39, 40].oA—not soft (hard) texture and MPD > 3 mmoB—not-soft (hard texture and MPD ≤ 3 mmoC—soft texture and MPD > 3 mmoD—soft texture and MPD ≤ 3 mmComparing R-MIPD and OPD for the primary outcome CCI®, time to functional recovery, and other outcomesComparing L-MIPD and OPD for the primary outcome CCI®, time to functional recovery, and other outcomesComparing R-MIPD and L-MIPD for the primary outcome CCI and time to functional recovery 

A detailed statistical analysis plan will be drafted prior to database lock of the short-term outcomes (up to 90 days postoperative). Despite all prior preventive measures taken, a complex international trial may evoke unforeseen situations after database lock that threaten data integrity and can only be resolved by unlocking the database prior to the final analysis. For purpose of transparency and reproducibility, the statistical analysis plan will therefore also describe the procedure to be followed when such situations arise.

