### Randomization

Patient recruitment and the collection of written informed consent are performed at the outpatient clinic. Hereafter, all patients will be randomized centrally by the study coordinators using an online computer controlled permuted-block randomization module (Castor EDC, CIWIT B.V., Amsterdam, the Netherlands). Randomization between MIPD and OPD will be performed in a 2:1 ratio, with block sizes varying between 3, 6, and 9 patients. The entire randomization process will be concealed to all involved investigators, except the study coordinator. Randomization will be stratified for the minimally invasive technique (laparoscopic or robotic), the pre-operative risk of post-operative pancreatic fistula (normal versus high risk, based on BMI (< 25 kg/m^2^ and ≥ 25 kg/m^2^) and pancreatic duct diameter (< 3 mm or ≥ 3 mm) on pre-operative imaging), and for the indication (pancreatic ductal adenocarcinoma (PDAC) or other indication). Patients will be coded by a numeric randomization code, and the study coordinator will be the only one with access to it. The source data will be stored digitally and will be kept by the project leader for 15 years after the last patient’s follow-up is completed.

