### Statistical aspects

#### Sample size calculation

The DIPLOMA-2 trial is designed as a non-inferiority trial, hypothesizing that the mean CCI® score of MIPD is non-inferior to OPD. Calculations are based on results of the pan-European E-MIPS retrospective cohort study and on individual patient-data collected from the previous conducted RCTs on MIPD versus OPD. The sample size is calculated using PASS 2022 software to achieve 80% power (1-β) in a per-protocol analysis with the following assumptions: 2.5% one-sided significance level (α), expected difference of the mean CCI® score in the MIPD and OPD group of 0 points, and a non-inferiority margin of 7.5 points, standard deviation of 20 points in both groups, including 5% metastasized disease, a 10% conversion rate and a 3% lost-to-follow-up rate after randomization leads to a total number of patients to be randomized of 288 (192 in the MIPD study arm and 96 in the OPD study arm). For time to functional recovery, we assume MIPD will result in a reduction of 2 days (7 days in the MIPD group versus 9 days in the OPD group. Time to functional recovery will be measured in days and will be tested for superiority using the Wilcoxon (Gehan-Breslow) test or the log-rank test (based on non-normal distribution). With a one-sided testing, assuming 5% metastatic disease, 10% conversion rate, and 3% loss to follow-up, a sample of 247 patients (159 in the MIPD group and 88 in the OPD group) in a per protocol analysis achieves 80% power to detect a 28% reduction of time to functional recovery (i.e., 6.5 days in the MIPD group; hazard ratio = 0.72). The estimated median time to functional recovery of 9 days in the OPD group is based on results of the LEOPARD-2 trial and corresponds to a median TTFR reduction of 2.5 days.

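### Randomisation is stratified by technique, fistula risk and indication, but the CCI non-inferiority test ignores these factors, so its interval is conservative and a modest gain in power goes unused

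*Protocol article*

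**What the plan says.** The Randomization section of the protocol article states: "Randomization will be stratified for the minimally invasive technique (laparoscopic or robotic), the pre-operative risk of post-operative pancreatic fistula" (normal or high), "and for the indication (pancreatic ductal adenocarcinoma (PDAC) or other indication"). Three two-level factors give eight cells. Allocation "will be performed in a 2:1 ratio, with block sizes varying between 3, 6, and 9 patients".

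The Statistical analysis section says that the CCI "will be tested for non-inferiority using independent samples" t-test or a Mann-Whitney U test, depending on distribution. Time to functional recovery "will be tested for superiority using the Wilcoxon (Gehan-Breslow) test or log-rank test, depending on the distribution". Neither statement brings in the stratification factors.

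The same section adds that "multivariable analyses will be performed to determine predictors for primary and secondary study outcomes". Those models look for predictors; they are not described as estimating an adjusted treatment effect. The planned subgroup comparisons split patients by technique or diagnosis and do not adjust the primary comparison either.

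The article announces a detailed statistical analysis plan before database lock of the short-term outcomes. It does not say that the treatment comparison will be adjusted there.

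**The concern.** Stratified blocks balance the factors between arms. Whatever CCI variance lies between strata then largely drops out of the true sampling error of the difference in means. An ordinary two-sample t-test still counts that variance in its standard error. The test is therefore conservative: its true one-sided error falls below 2.5%, and its 95% interval covers more than 95% of the time.

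There is reason to expect at least one prognostic factor. The article lists pancreatic fistula among the postoperative outcomes and describes the CCI as accumulating all complications, so a fistula-risk factor should carry some information about the CCI. In a non-inferiority trial planned at 80% power, an interval wider than necessary makes it somewhat harder to clear the margin.

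**Working it through.** **Inputs from the Sample size calculation section.** "2.5% one-sided significance level (α), expected difference of the mean CCI® score in the MIPD and OPD group of 0 points"; margin 7.5 points; SD 20 in both arms; planned "to achieve 80% power (1-β) in a per-protocol analysis"; 288 randomised (192 and 96); 5% metastasised, 10% conversion, 3% lost. The per-protocol counts 159 and 88 are given there for time to functional recovery.

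**Input that is assumed.** R2, the share of CCI variance explained by the three factors, shown from 2% to 15%.

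**Reproducing the plan.** With conversion applied to the MIPD arm only:
- MIPD: 192 × 0.95 × 0.90 × 0.97 = 159.2
- OPD: 96 × 0.95 × 0.97 = 88.5

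This matches 159 and 88. Then SE = 20 × √(1/159 + 1/88) = 2.657, the 95% half-width is 1.96 × 2.657 = 5.21 points, and power is Φ(7.5/2.657 − 1.96) = Φ(0.862) = 80.6%. The stated design is confirmed.

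**Formulas when strata are balanced and explain R2.** Let s = √(1 − R2).
- Adjusted power: Φ(7.5/(SE × s) − 1.96)
- True power of the unadjusted test: Φ((7.5/SE − 1.96)/s)
- True one-sided error of the unadjusted test: 1 − Φ(1.96/s)
- Narrowing of the interval: 1 − s

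**Per protocol, 159/88** (gains taken before rounding)

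| R2 | Unadjusted power | Adjusted power | Gain (points) | Adjusted half-width | Unadjusted one-sided error |
|---|---|---|---|---|---|
| 0% | 80.6% | 80.6% | 0 | 5.21 | 2.50% |
| 2% | 80.8% | 81.4% | 0.5 | 5.16 | 2.39% |
| 5% | 81.2% | 82.5% | 1.3 | 5.08 | 2.22% |
| 10% | 81.8% | 84.5% | 2.7 | 4.94 | 1.94% |
| 15% | 82.5% | 86.5% | 3.9 | 4.80 | 1.68% |

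The narrowing is 1.0, 2.5, 5.1 and 7.8% at R2 of 2, 5, 10 and 15%.

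**Modified intention-to-treat, 186/93.** This assumes that only the 3% loss removes patients (192 × 0.97 and 96 × 0.97). SE = 2.540 and power at R2 = 0 is 84.0%. At R2 of 5, 10 and 15% the unadjusted power is 84.6, 85.2 and 85.9%, the adjusted power 85.8, 87.5 and 89.3%, and the gain about 1.2, 2.3 and 3.4 points.

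**Simulation check for the CCI.** 6,000 runs per setting, normal outcomes, 247 patients, blocks of 3, 6 and 9 within eight strata. At R2 = 10% the unadjusted test had power 80.7%, one-sided error 1.95% and coverage 96.5%. The adjusted test had 84.0%, 2.5% and 95.5%. The simulated arms split about 165/82 rather than 159/88, so absolute power differs slightly from the table.

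**Time to functional recovery.** 4,000 runs per setting, exponential times, no censoring, hazard ratio 0.72, 247 patients. The one-sided 5% level is an assumption. A log-rank test stratified over all eight cells was compared with the unstratified test:

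| Stratum effect | Unstratified power | Stratified power | Change (points) |
|---|---|---|---|
| None | 77.2% | 74.8% | −2.4 |
| Weak | 75.6% | 74.3% | −1.3 |
| Moderate | 72.4% | 73.0% | +0.6 |
| Strong | 69.5% | 73.7% | +4.2 |

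**The case against.** Four objections deserve an answer.

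**The size.** One could set adjusted power against the 80.6% that applies at R2 = 0 and read off gains of 2.0, 3.9 and 5.9 points at R2 of 5, 10 and 15%. That comparison is unfair. If the strata are prognostic, balanced allocation already raises the power of the unadjusted test, to 81.2, 81.8 and 82.5%. For the same reason it would be wrong to say that stratification brings the trial nothing without adjustment.

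**Validity.** A reader might infer that the trial is underpowered or its test invalid. The documents do not support this. The stated 80% reproduces, the unadjusted test keeps it at any R2, and its one-sided error stays at or below 2.5%. The conservatism does not favour a non-inferiority claim.

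**The assumed input.** R2 is nowhere in the documents, and the article gives no reason for choosing these factors. This stands: the direction is established, the size is conditional.

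**Deferral to the analysis plan.** Covariate adjustment is often settled in the statistical analysis plan, and nothing in the article forbids it. This is fair, but the article names specific tests rather than staying silent, so the stated choice can be reviewed.

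Two extensions are tempting and do not hold. It cannot be said that stratifying the log-rank test would reliably raise power for time to functional recovery: over eight cells it can lower it. Nor is centre a case of a stratification factor left out of the analysis. It was not a stratification factor, each centre must give both arms the same postoperative care, and no figure supports a centre effect.

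**Conclusion.** The point holds as a modest, avoidable loss of efficiency on the primary outcome. The interval for the CCI difference is conservative to the extent that the three factors predict the CCI.

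Under assumed R2 of 5 to 15%, adjustment is worth about 1.3 to 3.9 points of power per protocol and 1.2 to 3.4 in the modified intention-to-treat set. At 2% it is worth about half a point. These figures rest on SD 20, the 7.5-point margin, a true difference of zero, the sample counts shown, normal approximations and near-balance within strata.

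For time to functional recovery the direction of any gain from full stratification is uncertain, so no loss of power is claimed there.

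**What to change.** Before database lock, specify the primary analysis as a linear model of CCI on arm plus technique, fistula-risk group and indication, using the values entered at randomisation, with robust standard errors. Compare the 95% confidence interval of the adjusted mean difference (MIPD minus OPD) with the 7.5-point margin. Keep the unadjusted result as a sensitivity analysis.

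For time to functional recovery, use a Cox model with the three factors as covariates rather than a log-rank test stratified over all eight cells. Centre may be added as an optional sensitivity analysis.

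The cost is wording in the statistical analysis plan. The three factors are already recorded for randomisation, and no new data or patients are needed.

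### The superiority test for time to functional recovery is left open between two rank tests, with a selector that cannot choose between them; this permits modest error inflation but does not by itself cause it

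*Protocol article*

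**What the plan says.** The Statistical analysis section states that time to functional recovery "will be tested for superiority using the Wilcoxon (Gehan-Breslow) test or log-rank test, depending on the distribution". The Sample size calculation section names the same pair with a slightly different reason: "using the Wilcoxon (Gehan-Breslow) test or the log-rank test (based on non-normal distribution".

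The only description of how a distribution is judged is general, in the Statistical analysis section: "The distribution of variables will be determined using several plots (boxplot, Q-Q plot and histogram) and the Kolmogorov–Smirnov and Shapiro–Wilk tests". The article does not say which finding leads to which test, whether the data are examined pooled or by arm, or whether the person choosing is blinded.

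The Discussion and Conclusion both present the trial as powered for this outcome. The power statement reads "a sample of 247 patients (159 in the MIPD group and 88 in the OPD group) in a per protocol analysis achieves 80% power" for a hazard ratio of 0.72 (6.5 against 9 days). It is introduced by "With a one-sided testing, assuming 5% metastatic disease, 10% conversion rate, and 3% loss to follow-up" and gives no significance level of its own. The primary outcome uses "2.5% one-sided significance level (α", and the general rule is "A two-tailed *p*-value < 0.05 will be considered statistically significant".

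**The concern.** Superiority on recovery is half of the trial's stated hypothesis, so its test should be fixed. As written it is not, and the stated selector does not fit the two candidates. Normality, or its absence, is irrelevant to both tests. Declaring the data non-normal, as the sample size section already does, rules out neither. A selector that cannot discriminate leaves the choice to discretion.

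The choice has content. Log-rank weights every event time equally. Gehan-Breslow weights each event time by the number still at risk, so the first days count most. In this trial that also shifts weight between the period when the patient is still blinded (up to postoperative day 5) and the period afterwards.

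Two things are at stake: which treatment contrast the superiority claim refers to, and whether its error rate is the nominal one if the choice is made with the arm comparison in view.

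**Working it through.** **1. The plan's own figure.** Inputs from the Sample size calculation section: 192 and 96 randomised, 5% metastatic disease, 10% conversion, 3% loss, hazard ratio 0.72.

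- Attrition: 192 × 0.95 × 0.90 × 0.97 = 159.2 and 96 × 0.95 × 0.97 = 88.5, which matches 159 + 88 = 247.
- Log-rank power (Schoenfeld), counting all 247 as events: Φ(√(d·p·(1−p))·|ln HR| − z), with d = 247, p = 159/247 = 0.644 and |ln 0.72| = 0.3285. √(247 × 0.644 × 0.356) = 7.53, and 7.53 × 0.3285 = 2.473.
- One-sided 5%: Φ(2.473 − 1.645) = 79.6%, the stated 80%.
- One-sided 2.5% or two-sided 5%: Φ(2.473 − 1.960) = 69.6%. The Freedman variant with unequal allocation gives at most 73%.

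So the stated power is what a log-rank calculation gives at one-sided 5%. Because the article does not settle the level for this outcome, error rates are shown at each candidate level.

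**2. How the tests differ.** Both have the form Z = Σ wⱼ(d₁ⱼ − dⱼn₁ⱼ/nⱼ) / √(Σ wⱼ²vⱼ). Log-rank has wⱼ = 1; Gehan-Breslow has wⱼ = nⱼ, the number at risk. Normality does not enter either statistic.

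**3. False-positive rate by selection rule.** Null simulation: 159 against 88 patients, whole days, median about 9 days, about 3% censored, 20,000 trials for each of three assumed shapes (exponential, lognormal, near-normal). Simulation standard error is √(0.025 × 0.975/20,000) = 0.11 points at 2.5%, and about 0.15 at 5%. The two Z statistics correlate at 0.87 to 0.91.

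| How the test is chosen | Nominal one-sided 2.5% | Nominal one-sided 5% |
|---|---|---|
| One test fixed in advance | 2.2–2.4% | 4.5–4.9% |
| Pooled shape (Shapiro–Wilk or skewness) | 2.2–2.5% | 4.5–5.0% |
| Proportional-hazards check between arms, 5% level | 2.5–2.6% | 5.0% |
| Early or late shape of the arm difference | 3.1–3.2% | 6.1–6.4% |
| Better of the two p-values | 3.3–3.5% | 6.5–6.7% |

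At two-sided 5%, the better of the two gives about 7.4% (lognormal times, no censoring).

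**4. Analytic check of the worst case.** P(max(Z₁, Z₂) > c) = 1 − Φ₂(c, c; ρ). For ρ = 0.95 this is 3.2% (nominal 2.5%) and 6.3% (nominal 5%). For ρ = 0.80 it is 3.9% and 7.5%. The simulated values lie inside these ranges.

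**5. Does the choice matter when the planned effect is real?** Medians 6.5 against 9 days, 159 against 88, 3% censoring, two-sided 5%, 6,000 trials, shapes assumed:

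- Exponential times: power is 67% for log-rank and 54% for Gehan-Breslow, and the tests disagree on significance in 19% of trials.
- Lognormal times with a wide spread (standard deviation 0.8 on the log scale): about 76% and 82%, with 13% disagreement.
- Lognormal times with a tighter spread (0.6 on the log scale): both powers exceed 95%, with disagreement in about 4%.

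Neither test is uniformly better. How often the choice decides the result depends on a shape that the article does not give.

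**The case against.** A reader might infer that the rule inflates the false-positive rate because the test is picked after the results are seen. The article does not say that. The plots and normality tests it lists describe the shape of a variable; they do not compare arms. On pooled data such a screen is merely an irrelevant selector between two valid tests, and the table shows error at nominal. Even a formal proportional-hazards check between arms costs almost nothing. The better-of-two figures model a rule that the article does not state, so they are an upper bound. All of this stands.

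It can also be said that a detailed analysis plan is to be drafted before lock of the 90-day data and may name the test. That is true and limits the severity. The point, however, concerns a rule that the article does state and that cannot work; an analysis plan that carried it over would inherit it.

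The timing of any benefit could be judged from earlier trials, without this trial's unblinded data. That also stands, and it supports fixing the test in advance.

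Lastly, the hazard ratio does not prove a commitment to log-rank: 0.72 is simply 6.5/9, and both tests are named just before it. Preferring log-rank is a matter of consistency with the power statement. Naming either test would cure the defect.

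**Conclusion.** The point holds in limited form. The test for the trial's main secondary outcome is open between two candidates, and the stated criterion cannot separate them. Nothing in the article requires the choice to be pooled or blinded, so inflation is permitted but is not a necessary result.

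Its size runs from none, for a pooled choice, to the worst case of 3.2 to 3.9% at one-sided 2.5%, 6.3 to 7.5% at one-sided 5%, and about 7.4% at two-sided 5%. The correlation between the tests, the distribution shapes and the 3% censoring are assumptions. The worst case changes little across them; the frequency of disagreement under the planned effect changes a good deal (about 4 to 19%).

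For a secondary outcome with a modest upper bound, this should be corrected, but it does not threaten the primary conclusion.

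**What to change.** Before any unblinded look at recovery data, name one primary test for time to functional recovery in the protocol and the analysis plan. One suitable choice is the log-rank test stratified by the factors in the Randomization section (minimally invasive technique, pancreatic fistula risk, indication), reported with the matching stratified hazard ratio. This agrees with the hazard ratio in the power statement and with the stratified design. List Gehan-Breslow as a sensitivity analysis, and delete the clause that makes the choice depend on the distribution, together with its counterpart in the sample size section. State the sidedness and level of the test in the same sentence.

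The cost is about one sentence in each document. The statistical price is some loss of sensitivity if the benefit is confined to the first days. If the team expects that pattern on prior evidence, naming Gehan-Breslow instead, with the reason given, would equally close the gap.

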### Primary outcome

The primary outcome is the Comprehensive Complication Index (CCI®), measured up to 90 days post-operatively. The CCI® score is developed to reflect the postoperative morbidity based on the Clavien-Dindo classification of postoperative complications and is validated for pancreatic surgery [23–25]. The CCI® score ranges from 0 (no complication of any kind during the postoperative period) and 100 (death of patient). The advantage of the CCI® over the Clavien-Dindo classification is the ability to accumulatively assess the postoperative morbidity considering all complications instead of only scoring the “most severe” complication. Repeat Clavien-Dindo 1 complications will be counted only once (i.e., not be scored cumulatively) in the CCI.

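### The confidence-interval rule for the primary outcome uses a difference in proportions, which CCI does not have, and names the lower limit without fixing the subtraction order or the sign of the margin

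*Protocol article*

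**What the plan says.** Primary outcome section: "The CCI® score ranges from 0 (no complication of any kind during the postoperative period) and 100 (death of patient"). Higher is therefore worse.

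Sample size calculation: the trial is planned by "hypothesizing that the mean CCI® score of MIPD is non-inferior to OPD", with "expected difference of the mean CCI® score in the MIPD and OPD group of 0 points, and a non-inferiority margin of 7.5 points". The SD is 20 points in both groups, alpha is 2.5% one-sided, and the size is set "to achieve 80% power (1-β) in a per-protocol analysis". The margin is given as a plain 7.5, without a sign. The Abstract repeats the mean difference and the margin.

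Statistical analysis: CCI is to be tested for non-inferiority with a t-test or a Mann-Whitney test, depending on its distribution. A little further on, for the primary outcome, "the lower limit of the two-sided 95% confidence interval of the difference in proportions will be reported and compared with the non-inferiority margin". The outcome that the same section does express in proportions is major complications, which is secondary.

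**The concern.** The sentence has two separate problems.

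1. **Effect measure.** A difference in proportions does not exist for a continuous score. It contradicts the hypothesis on the mean, the SD, the margin in points and the t-test.
2. **Limit and sign.** On a harm score, the limit that rules out excess harm is the upper one if the difference is MIPD minus OPD. It is the lower one if the difference is OPD minus MIPD and the margin is -7.5. The article states neither the order nor a signed margin. It also does not say on which side of the margin the limit must fall.

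This is the only place where the article ties a confidence interval for the primary outcome to the margin. The trial was set up to settle a safety question, so its success criterion should allow one reading only.

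**Working it through.** **Inputs.** Margin 7.5, SD 20, expected difference 0, one-sided alpha 0.025, power 80%, and losses of 5% (metastasized), 10% (conversion) and 3% (follow-up), all from Sample size calculation; 2:1 allocation, from Design. Analysed numbers are taken two ways:

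- 159/88, the per-protocol numbers that the article gives for time to functional recovery under the same losses.
- 186/93, an assumption: 192 and 96 less 3% only.

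**Step 1: is the design one for means?**

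- OPD evaluable = (1 + 1/2) × [20 × (1.960 + 0.842)/7.5]² = 83.7, so 84 OPD + 168 MIPD = 252.
- Losses by arm, with conversion in MIPD only: 192 × 0.95 × 0.90 × 0.97 = 159 and 96 × 0.95 × 0.97 = 88. These match the stated 159/88.
- SE = 20 × √(1/159 + 1/88) = 2.657. Power = Φ(7.5/2.657 − 1.96) = 80.6% (80.3% by noncentral t), against 80% stated.

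The stated 288 (192 + 96) is therefore consistent with a difference in means, with conversion losses in the MIPD arm only. Applying all three losses to both arms would give 252/(0.95 × 0.90 × 0.97) = 304.

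**Step 2: could 7.5 mean percentage points?** The article gives no event rate. With assumed equal rates of 20% to 50%, 80% power would need about 1005 to 1572 evaluable patients, and 159/88 would give about 29% down to 20% power. The design was not made for proportions.

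**Step 3: what the lower limit would do on the mean scale.** Let D be the true mean CCI for MIPD minus OPD, with 159/88 analysed (SE 2.657, normal approximation).

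| Rule for concluding non-inferiority | Probability at D | D = 0 | D = 7.5 |
|---|---|---|---|
| MIPD − OPD, upper limit < +7.5 | Φ((7.5 − D)/SE − 1.96) | 80.6% | 2.5% |
| (a) MIPD − OPD, lower limit < +7.5 | Φ((7.5 − D)/SE + 1.96) | about 100% | 97.5% |
| (b) MIPD − OPD, lower limit > −7.5 | Φ((7.5 + D)/SE − 1.96) | 80.6% | 99.99% |
| (c) OPD − MIPD, lower limit > +7.5 | Φ(−(7.5 + D)/SE − 1.96) | about 0 | about 0 |
| (d) OPD − MIPD, lower limit > −7.5 | same as the upper-limit rule | 80.6% | 2.5% |

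Of the four lower-limit readings only (d) is a valid non-inferiority rule, and it needs an order and a negative margin that are not written.

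**Step 4: size under reading (a).**

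| True harm | 159/88, SE 2.657 | 186/93, SE 20 × √(1/186 + 1/93) = 2.54 | Upper-limit rule |
|---|---|---|---|
| 7.5 | 97.5% | 97.5% | 2.5% |
| 10 | 84.6% | 83.5% | about 0.2% |
| 12.5 | 53.1% | 49.7% | 0.01% or less |

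The choice of analysed number hardly matters.

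**The case against.** The strongest reply is that the lower limit has not been shown to be an error. A margin quoted as 7.5 may be a magnitude, and with OPD minus MIPD against -7.5 the lower limit is exactly right: 2.5% error and 80.6% power. This stands. The fault in that half of the sentence is that sign and order are undefined, not that the limit is wrong under every convention.

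A reader might also infer that the plan, followed as written, would pass a harmful operation as non-inferior. The article does not support that. It says only that the limit is compared with the margin and gives no inequality. As written, the rule cannot be applied to CCI at all. Reading (a) requires replacing proportions by means, choosing MIPD minus OPD, and choosing *below*.

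Nor is this sentence the sole basis for a conclusion. The hypothesis on the mean, the one-sided alpha, the margin and the t-test together already make a workable test, and that test agrees with the correct interval rule. The CI sentence conflicts with it.

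Finally, the wording looks like a drafting slip, and a detailed statistical analysis plan is promised before database lock. That plan may well put it right. But the sentence states a wrong rule rather than leaving a detail open, and no correct interval rule appears elsewhere in the article. An analysis plan that follows it inherits the error; one that departs from it disagrees with the published protocol.

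**Conclusion.** The point holds as an internal contradiction in the primary decision rule. The difference in proportions is wrong under any reading. The lower limit is undetermined, because order and sign are missing, and it is the wrong limit for MIPD minus OPD with +7.5.

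The 97.5%, 84-85% and 50-53% figures apply only if the rule were used as reading (a). They assume an SD of 20, a normal approximation and 159/88 or 186/93 analysed. They show what the ambiguity could cost; they do not predict what the trial will do. The sample size of 288 is not affected. Because this is the primary criterion of a safety trial and the repair is trivial, it should be corrected.

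**What to change.** Replace the sentence with: *The difference in mean CCI (MIPD minus OPD) will be estimated with a two-sided 95% CI; non-inferiority is concluded if the upper limit is below +7.5 points.*

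Add that this interval governs the primary conclusion whatever the distribution of CCI. The Mann-Whitney test should be supportive only, because it gives no interval on the mean scale on which the 7.5-point margin is set. Without this addition, a competing primary test would remain.

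Cost: these lines in the statistical analysis plan and a protocol clarification before database lock. No extra patients, no new data and no change to the sample size.
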